# The impact of elder abuse training on subacute health providers and older adults: study protocol for a randomized control trial

**DOI:** 10.1186/s13063-024-08160-3

**Published:** 2024-05-22

**Keywords:** Elder abuse, Training, Older people, Subacute, Intervention, Co-design, Pragmatic trial

## Abstract

**Background:**

Elder abuse often goes unreported and undetected. Older people may be ashamed, fearful, or otherwise reticent to disclose abuse, and many health providers are not confident in asking about it. In the *No More Shame* study, we will evaluate a co-designed, multi-component intervention that aims to improve health providers’ recognition, response, and referral of elder abuse.

**Methods:**

This is a single-blinded, pragmatic, cluster randomised controlled trial. Ten subacute hospital sites (i.e. clusters) across Australia will be allocated 1:1, stratified by state to a multi-component intervention comprising a training programme for health providers, implementation of a screening tool and use of site champions, or no additional training or support. Outcomes will be collected at baseline, 4 and 9 months. Our co-primary outcomes are change in health providers’ knowledge of responding to elder abuse and older people’s sense of safety and quality of life. We will include all inpatients at participating sites, aged 65 + (or aged 50 + if Aboriginal or Torres Strait Islander), who are able to provide informed consent and all unit staff who provide direct care to older people; a sample size of at least 92 health providers and 612 older people will provide sufficient power for primary analyses.

**Discussion:**

This will be one of the first trials in the world to evaluate a multi-component elder abuse intervention. If successful, it will provide the most robust evidence base to date for health providers to draw on to create a safe environment for reporting, response, and referral.

**Trial registration:**

ANZCTR, ACTRN12623000676617p. Registered 22 June 2023.

**Supplementary Information:**

The online version contains supplementary material available at 10.1186/s13063-024-08160-3.

## Introduction

Elder abuse refers to harm caused to an older person by a single or repeated act within a relationship of trust. It can include financial, physical, psychological, sexual abuse, and neglect [1, 2] and is commonly perpetrated by adult children [3]. Elder abuse is associated with increased morbidity and mortality including higher rates of depression, anxiety, fear, stress, substance dependence, social isolation, poorer physical health, and suicide [4–6]. Community prevalence is around 15% [1], although rates of underreporting are high [7].

Specialised health, aged care, community, and legal services directly involved in care for older people experiencing abuse hold valuable expertise about recognising and responding to elder abuse [8]. However, many frontline health providers do not recognise elder abuse, do not report suspected cases, and often lack the time, confidence, and knowledge to respond [9, 10]. Additionally, ageist attitudes amongst health providers may impede older people’s care [11]. Ageism is a recognised driver of elder abuse as it perpetuates notions that older people are dependent, an economic burden, and have less relevance, which in turn lead to greater tolerance of abuse [12].

Reviews [13, 14] consistently identify the most effective interventions to stop and prevent further occurrence of elder abuse include educating health providers and involving multidisciplinary services. The few randomised control trials (RCTs) in this area mostly focus on one of these interventions, demonstrating that training health providers can improve awareness and knowledge elder abuse response [15, 16] and improve how student practitioners detect financial elder abuse [17]. Evidence regarding the impact of training on health providers’ attitudes, detection, and reporting rates within health services is sparse [10, 18, 19].

We aim to test whether a multimodal intervention combining health provider training, provision of a screening tool, and a site champion improves health providers’ knowledge and management of abuse and older people’s sense of safety and quality of life over 9 months, compared to no additional training or support in Australian subacute hospitals.

Subacute hospitals provide multidisciplinary care to optimise functioning and quality of life, including rehabilitation, geriatric evaluation and management, psychogeriatric care [20], and often involve longer stays to manage complex health conditions before discharge. This provides an important opportunity for clinicians to build trust [8]. This may be the only time an older person experiencing abuse leaves their home for a prolonged period, spending time away from the perpetrator. Indeed, the abuse itself may precipitate or prolong their hospital stay [21].

### Aims and hypotheses

*Our primary aim *is to test the hypothesis that health providers in the intervention arm will show greater knowledge of responding to elder abuse at 4 months relative to the control arm and that older adults in the intervention arm will show greater quality of life at 4 months than those in the control arm.

## Methods

### Design and theory

This is a pragmatic, cluster RCT. The intervention is guided by the Theory of Change [22], which seeks to create a safe and inclusive relationship between health providers and older people (see Fig. 1). We use the SPIRIT reporting guidelines (see Additional file 1) [23].

**Fig. 1 Fig1:**
[figure not shown]
Our intervention is guided the Theory of Change [22]. We conceptualise stigma as an interpersonal, social phenomenon. Our intervention reduces this stigma by creating a safe and inclusive relationship between health providers and older people. Through staff training, educating and modelling; implementation of a screening tool; and champions to sustain processes; we create, measure, and sustain practice change

### Participants and setting

#### Sites

Subacute hospitals providing inpatient care in New South Wales, South Australia, Victoria, and Western Australia were included.

#### Health providers

We aim to recruit inpatient subacute clinical staff providing direct care to older people, including medical, nursing, or allied health. We will exclude staff who do not expect to be working at the site for at least 12 months post-baseline or who participated in co-designing the training.

#### Older people

We will include all inpatients at participating sites, aged 65 + (or aged 50 + if Aboriginal or Torres Strait Islander), who are willing to participate and individually capable of providing informed consent.

Exclusion criteria for older people are (i) receiving palliative care and (ii) lack of decision-making capacity.

### Intervention

This intervention comprises 3 components:(i)*Training*: Health provider participants will be asked to complete training via an online Learning Management System (Acorn) hosted by the National Ageing Research Institute (NARI). The training takes ~ 60 min to complete and is self-paced, and participants will have access to it over a 2-month period. It has four modules on knowledge of abuse, drivers of abuse, screening for abuse (including how to administer the Australian Elder Abuse Screening Instrument [AUSI]) [24], and management of elder abuse (further details available through the online trial registry anzctr.org.au, registration #ACTRN12623000676617p). This training was co-designed through workshops, interviews, and user-testing with health providers, family carers, older people, and elder abuse survivors. Site champions will promote completion of the training, with the aim of at least 60% of eligible health providers on participating wards completing the training over a 2-month period.(ii)*Screening tool*: Intervention sites will be provided with the AUSI screening tool, which has content validity [24], and has been demonstrated to increase staff confidence in screening for abuse and the proportion of cases of suspected abuse that provoked multidisciplinary responses [25]. Following the training, health providers will be asked to screen all patients for elder abuse and to manage detected cases as per usual practice, including referrals to outside agencies, but with support from the site champion where required.(iii)*Site champion*: Each site will recruit an on-site clinician (senior social worker or other staff with commensurate experience) as a site champion, who will support other hospital staff in screening and managing elder abuse. They will be trained by the research team and work 1 day per week supporting the intervention. Site champions will encourage uptake of the training and the AUSI and regularly contact staff to assess concerns and/or challenges encountered with screening. Site champions will be contacted every 2–3 weeks via email/phone by the research team to proactively support them and build a national peer-support network [26].

### Control

The control arm will be waitlisted and given access to the training after 9 months. Control arm sites will also recruit site champions, who will be trained and supported in data collection. They will encourage completion of the outcome measures for health providers, recruit older people and collect data, and collect deidentified site data but will not provide further input beyond their normal clinical role.

### Outcome assessments

All health provider participants will complete baseline assessment prior to site randomisation. Outcomes will be assessed at baseline (t0), 4 months follow-up (t1), and 9 months follow-up (t2) (see Table 1).

#### Sites

Site champions will obtain summary statistics routinely collected by hospitals such as general site characteristics (size of workplace, location, subacute services offered) and characteristics of patients admitted to participating wards (age, gender, country of birth, English proficiency, reason for subacute stay). They will also ascertain the number of eligible health providers to enable the calculation of the percentage who complete the training. Elder abuse detection and referral data will be collected from the 9 months preceding the trial to the end of the trial (i.e. at completion of 9-month outcomes). Specifically, site champions will screen medical records of all inpatients on participating wards during that time to ascertain (i) number of records screened, (ii) number of cases that identified elder abuse and the types, (iii) referrals made to social work, and (iv) the frequency of interventions and referrals (e.g. legal referral, safety planning) using a standardised template that will be provided. In the intervention arm, the number of times the AUSI screening tool is administered and not administered will also be collected; however, the responses on the AUSI will not be collected.

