#### Health providers

Health providers will complete a demographic survey (age, gender, profession, years of experience in profession, and whether they have completed elder abuse training prior to the trial). They will also complete the adapted Knowledge and Management of Abuse (KAMA) [27] (primary outcome) adapted for an Australian subacute care setting, the Australian adaptation of the Caregiver Scenario Questionnaire (CSQ) [28, 29], and Carolina Opinions on Care of Older Adults (COCOA) survey [30] (secondary outcomes) via online survey in REDCap.

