	**Older adults**				
	** Informed consent**	**x**			
	** Demographic Information**		**x**		
	** ASCOT questionnaire**		**x**	**x**	**x**
	** SF-12v2 questionnaire**		**x**	**x**	**x**
	** a-RUD-lite questionnaire**		**x**	**x**	**x**
	** Has patient attended another hospital in trial during study period**		**x**	**x**	**x**
	**Administrative/site data**	**9 months prior to Baseline**	**Baseline**	**Baseline to 4 months**	**4-months to 9 months**
	** Elder abuse cases**	**x**	**x**	**x**	**x**
	** Elder abuse referrals**	**x**	**x**	**x**	**x**
	** Nature of referral**	**x**	**x**	**x**	**x**
	** Number of eligible clinicians (total and by profession)**		**x**	**x**	
	** Number of clinicians who have completed the training (total and by profession)**		**x**	**x**	
	** Number of times the screening tool was administered/not administered**		**x**	**x**	**x**

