### Sample size

As health providers are not anticipated to be systemically different based on location (clusters), we have not accounted for ICC for health providers; therefore, we calculated that 60 health providers would be sufficient to detect a medium effect (Cohen’s *d* of 0.5) on the KAMA at a power of 80% and a significance level of 1%. This difference is similar to that reported in our previous research, and the sample size calculation uses a standard deviation of 4.8 as previously reported [34]. We calculated that we need 10 clusters (5 intervention, 5 control) with 40 older people in each cluster to detect a medium effect on the ASCOT at a power of 80% and a significance level of 5%. As responses to elder abuse vary across jurisdictions, an ICC of 0.1 is assumed for older people with the standard deviation of 0.2 reported by others [35], calculated using the Shiny Calculator for Sample size for Cluster Randomised Trials [36]. Assuming 53% refusal rate to participate/unable to consent as observed in our group’s prior work in the UK [37, 38], the total sample size is 92 health providers and 612 older people (~ 60 older people/site).

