### Analysis

#### Primary and secondary RCT outcomes

The primary analysis will be performed according to intention to treat, including all clusters and participants in the allocated groups. Between-group difference for both primary outcomes (health provider and older people) will be analysed using mixed effects regression models with a fixed effect for the intervention group and random effect for participants to account for repeated measures. Cluster site will also be added as a random effect. Due to the likelihood of differences across sites, a number of baseline covariates will be controlled for in the analyses (as listed in Table 2).

**Table 2 Tab2:** List of covariates to be used in analysis and source

	*Health provider outcomes*	*Older adult outcomes*
*Self-reported*	Profession, age, gender, years in the role	Age, sex, ethnicity, location, educational and economic attainments, country of birth, English proficiency, reason for subacute stay, and admission to any other hospital in the trial
*Reported by site champion based on data routinely collected by hospitals, or case records*	General characteristics of the site (size of workplace, location, subacute services offered), average characteristics of older patient cohorts admitted to the participating wards (age, gender, country of birth, English proficiency, reason for subacute stay), and elder abuse cases (number of suspected elder abuse cases p/month, number, and types of referral) to enable the evaluation and statistical control of differences between sites	Length of hospital admission, length of admission on participating ward; number of eligible clinicians (total and by profession), and number of clinicians who have completed the training (total and by profession) to provide a measure of ‘dose’

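### Elder-abuse screening in usual care is not described as measured in either arm, and outside elder-abuse training is asked only at baseline and is not a listed covariate

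*Protocol article*

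**What the plan says.** **Screening activity.** The Sites part of Outcome assessments states: "In the intervention arm, the number of times the AUSI screening tool is administered and not administered will also be collected". In Table 1, under administrative and site data, the corresponding row reads "Number of times the screening tool was administered/not administered". It is marked at baseline and for both follow-up periods, and names neither the AUSI nor an arm.

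**Record review.** The same Sites text says "Elder abuse detection and referral data will be collected from the 9 months preceding the trial to the end of the trial", and that "site champions will screen medical records of all inpatients on participating wards during that time". Neither statement is confined to one arm, and the Control section has control champions collecting de-identified site data too. The items listed are the number of records screened, abuse cases and their types, social work referrals, and "the frequency of interventions and referrals (e.g. legal referral, safety planning) using a standardised template that will be provided".

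**Training outside the trial.** The Health providers part of Outcome assessments puts one question in the demographic survey: "whether they have completed elder abuse training prior to the trial". Table 1 schedules that survey at baseline only.

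**Adjustment.** Table 2 lists the self-reported covariates for provider outcomes as "Profession, age, gender, years in the role".

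**Site variation.** The Sample size section says "As responses to elder abuse vary across jurisdictions, an ICC of 0.1 is assumed for older people". For providers, the same section expects no systematic difference by location.

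**The concern.** The comparator is usual practice without added training or support, and the control arm waits until after 9 months for the trial training. Nothing in the article stops staff at a control site from taking other elder-abuse training, or from using some other screening method, in the meantime. In a pragmatic trial that is legitimate usual care, but it has to be known when the result is read.

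Suppose the arms end with similar KAMA scores at 4 months, or similar detection and referral counts. That pattern fits an ineffective intervention. It also fits an effective one set against control sites that were active on their own account. Detection and referral counts are downstream results and do not separate these explanations. Data on exposure would: how many patients were screened by any method, and how many providers trained elsewhere. With five control sites, one unusually active site is a fifth of the arm's clusters. A later analysis plan cannot recover exposure data that were never collected.

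The covariate is a separate and smaller matter. Prior elder-abuse training is a baseline measure with an obvious link to a knowledge score. It is collected and then left off the list of variables to be adjusted for.

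**Working it through.** The plan states no contamination rate or screening rate, so there is no figure to reproduce. The check sets the sections side by side.

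**1. What is recorded on screening, by arm**

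| Item | Intervention | Control | Source |
|---|---|---|---|
| AUSI administered / not administered | Yes | No, per the text; Table 1 names no arm | Sites; Table 1 |
| Elder-abuse screening by any other method | Not described | Not described | – |
| Abuse cases and types | Yes | Yes | Sites; Control |
| Social work referrals, interventions, other referrals | Yes | Yes | Sites; Control |

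The listed item on records screened should not be mistaken for patient screening. It counts the records that the champion reviewed.

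**2. What is recorded on training**

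| Item | When | Source |
|---|---|---|
| Completion of the trial training | Logged in the learning system; expressed as a site dose | Process evaluation; Recruitment |
| Elder-abuse training before the trial | Baseline only | Health providers; Table 1 |
| Elder-abuse training outside the trial during follow-up | Not described | – |

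The process-evaluation visits go to intervention sites only, so they do not fill the control-arm gap.

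**3. Timing of the prior-training item.** Outcome assessments and Group allocation both place the provider baseline before site randomisation. The item is therefore a true baseline variable and safe to adjust for. It is absent from Table 2. The Analysis section also adjusts continuous outcomes for baseline values, so baseline KAMA will already carry part of what prior training would explain.

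**4. Illustration of dilution (assumed, not derived).** Let c be the share of control providers who gain training elsewhere. Assume that this training is fully equivalent to the trial's and that outside training changes nothing in the intervention arm. The planned standardised difference for KAMA is 0.5 (Sample size).

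- Diluted effect = 0.5 × (1 − c)
- Factor by which the sample must grow to hold power = 1 / (1 − c)²

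| c (assumed) | Diluted effect | Sample factor |
|---|---|---|
| 10% | 0.5 × 0.9 = 0.45 | 1 / 0.81 = 1.23 |
| 20% | 0.5 × 0.8 = 0.40 | 1 / 0.64 = 1.56 |
| 30% | 0.5 × 0.7 = 0.35 | 1 / 0.49 = 2.04 |

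These figures show only that the unknown could matter. Partial equivalence, or outside training that also benefits the intervention arm, would shrink the dilution.

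**The case against.** A reader might infer that background screening is being counted in one arm only. The text does not support that. The AUSI count measures uptake of a tool that only intervention sites receive, so it is an adherence measure and belongs in that arm. Background screening is not described as counted in either arm.

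A reader might also infer that the trial could not show that the arms received different care. That is too strong. Cases, referrals and interventions are abstracted from 9 months before the trial to its end without limit to one arm. Trial training is logged and withheld from control sites until after 9 months. A between-arm comparison of detection, response and trial-training exposure is therefore available.

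Other points also carry weight:

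- Site differences are partly handled. State is a stratification factor, and Table 2 lists suspected cases per month and referrals as site-level covariates for provider outcomes.
- The statement on jurisdictional variation concerns older people. The protocol expects no such pattern for providers.
- Spread between trial sites is addressed. Staff are asked not to discuss the study elsewhere, and older people's attendance at another trial hospital is recorded at each time point. Neither measure covers training or screening from outside the trial.
- Baseline adjustment absorbs part of any imbalance in prior training.
- The article is condensed. The record-review template is not shown, and Table 1 lists instruments rather than survey questions, so either item may exist in the full forms.

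These points narrow the concern but do not remove it. What stands is that the items described omit screening by other methods and outside training during follow-up, that the Table 1 row and the Sites text differ in scope, and that a collected baseline variable is missing from a covariate list that the article does specify.

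**Conclusion.** The point holds as a limited and inexpensive improvement. As described, usual-care screening is measured in neither arm, outside training is not followed after baseline, and prior training is not among the provider covariates. The consequence is a weaker reading of a null result. It is neither a bias in the planned estimate nor a loss of the comparison between arms.

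The size cannot be derived from the documents. The diluted effects of 0.45 to 0.35 rest wholly on an assumed share of 10% to 30% and on full equivalence of outside training. The gain from the added covariate may be modest because baseline values are already adjusted for. The data-collection part of the point assumes that the unshown template and surveys contain no such items. If they do, what remains is the covariate and the Table 1 wording.

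**What to change.** 1. **Table 2:** add prior elder-abuse training, as reported at baseline, to the provider covariates for KAMA. The item is already collected, so this costs nothing.
2. **Sites text and Table 1:** add to the record-review template, in both arms and for the 9 months before baseline as well as the trial period, the number of patients with any documented elder-abuse screening, whether by the AUSI or otherwise. Keep the AUSI count as the adherence measure. State in the Table 1 row which tool and which arm it refers to, so that it agrees with the Sites text.
3. **4- and 9-month provider surveys, both arms:** add one item on elder-abuse training taken outside the trial since the previous survey. Report it descriptively by arm. Do not adjust for it, because it arises after randomisation and could itself be affected by allocation.

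The downside is slightly longer record abstraction and a slightly longer survey. Where follow-up has already begun, the screening field can still be completed from existing records, whereas the survey item will cover only the assessments that remain.
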